### Participant timeline

Participants are enrolled prior to or within 12 h of their CVAD insertion, and will continue on the study until 48 h after their CVAD is removed. It is anticipated that each CVAD will dwell for an average of 7 days, resulting in an average enrolment time for each participant of 9 days (including CVAD dwell whilst in ICU and on the ward).

### Sample size

A total of 160 patients will be recruited. At 90% power and a significance level of 0.05, 77 patients per group are required to detect a 25% absolute difference in the primary outcome (control failure 50%, intervention failure 25% [2]). To account for potential attrition, three additional patients per group will be recruited.

### Recruitment

Each participating site has been targeted as they have a track record of conducting efficient and accurate research within their ICUs. Site feasibility assessments (i.e. anticipated number of eligible patients, adequate staffing resources, clinical equipoise) were conducted at each site prior to study commencement. Each member of the research team at each site will be provided extensive education on the study protocol prior to recruitment commencement, and will be encouraged to notify the project manager of any recruitment difficulties to ensure strategies are in place to overcome these and ensure adequate participant enrolment.

### Assignment of interventions: allocation

#### Sequence generation

Patients will be randomised in a 1:1 ratio to either ‘standard’ dressing care or ‘standard’ dressing care in addition to MLA. Randomisation will occur in computer-generated randomly varied block sizes of four and six and will be stratified by patient sex to account for facial hair differences.

#### Concealment mechanism

Randomisation allocation will be concealed until the point of randomisation using a central, web-based randomisation service embedded within the study database.

#### Implementation

A statistician independent of the research team will generate the randomisation allocation sequence, and this will be uploaded onto the randomisation service without viewing by the research team. Patients will be enrolled and randomised by members of the research team, with intervention allocation assigned as per the randomisation service.

### Assignment of interventions: blinding

#### Who will be blinded

Due to the nature of the intervention, blinding of patients/clinicians and research staff to the intervention is not possible. However, the statistician will be blinded for analysis, and microbiology laboratory staff will be blinded when culturing swab growth. The infectious diseases consultant will also be blinded to treatment allocation when apportioning infection outcomes.

#### Procedure for unblinding

Not applicable. There will be no instances where it would be necessary to unblind the statistician, laboratory staff or infectious diseases consultant.

### Data collection and management

#### Plans for assessment and collection of outcomes

Patient demographic and CVAD insertion data will be collected by research staff at the time of patient enrolment (see Table 1). Research staff will perform daily assessments to collect data on the primary and secondary outcomes, protocol adherence and adverse events (see Fig. 1). To ensure accurate assessment of outcomes related to site complications and adverse skin events, a convenience sample of patients (*n* = 8 per group) will undergo inter-rater reliability assessments of site and skin complications. Research staff will also collect timing data for dressing changes (*n* = 10 per group) to inform cost estimates (see Secondary Outcome 13).

**Table 1 Tab1:** Data collection

Study enrolment	CVAD insertion	Daily check	CVAD removal	48 h post-CVAD removal
Age Weight Height APACHE II Score Skin type • Very fair, fair, medium, olive, etc. Skin integrity • Good, fair, poor Date of hospital and ICU admission ICU admission type • Planned, emergent, IHT Primary reason for ICU admission • Medical, surgical, other Number of comorbidities Current infections • Blood, urinary, respiratory, etc. Current wounds • Yes, no	CVAD insertion site • Left or right IJ Placement of CVAD in IJ vein • High, mid, low Angle of CVAD lumens • Down, up, horizontal Number of CVAD lumens Place of CVAD insertion • ICU, OT, etc. Antimicrobial-impregnated CVAD • Yes, no Inserter type • ICU registrar, ICU consultant, anaesthetic registrar, etc. Number of insertion attempts Technologies used during insertion • Ultrasound, x-ray, ECG, etc. Hair clipped prior to CVAD insertion • Yes, no Dressing site • Neck, chest, other Diaphoretic at insertion site • Yes, no Facial hair at insertion site • Yes, no Dressing and securements in addition to ‘standard care’ • Sutures, bordered transparent dressing, tissue adhesive, etc. Date and time of first MLA application Staff/patient satisfaction with dressing application • 0 = not at all satisfied, 10 = completely satisfied	Date/time of check Reason why check not able to be completed • Patient not available, etc. Is randomised dressing still in situ • Yes, no Dressing site • Neck, chest, other Dressing and securements in situ • Sutures, bordered transparent dressing, tissue adhesive, etc. Condition of current dressing • Clean, dry, intact, lifting at edges, etc. How many edges of the dressing are lifting or requiring reinforcement Complications at CVAD insertion site • Redness, purulent discharge, pain, etc. Has the patient mobilised, been diaphoretic, restless/agitated • Yes, no Signs and symptoms of skin injury/reaction • Pain, itch, redness, rash, papules, stripping, blister, etc. Suspected cause of MARSI or skin injury/reaction Extent of redness, rash or maceration if applicable Positive bloodstream infections since last daily check • Yes, no Number of administration sets What is the CVAD currently being used for • Fluids, blood products, CVP monitoring, blood sampling, etc. Dressing changes since last daily check • Date/time, reason for dressing change, staff/patient satisfaction, etc.	Date/time of CVC removal Reason for CVC removal • Treatment complete with/without complications, patient deceased, routine replacement, etc. Complications at time of CVC removal • Occlusion, unable to aspirate, accidental removal, suspected infection, MARSI, etc. Signs and symptoms of skin injury/reaction • Pain, itch, redness, etc. Extent of redness, rash or maceration if applicable Pain, tenderness, redness, swelling at CVC insertion site Patient mobility at time of CVC removal • Independent, requires assistance, bed-bound, etc. IV antibiotics administered during CVC dwell • Yes, no Patient diagnosed with delirium • Yes, no Staff/patient satisfaction with dressing removal • 0 = not at all satisfied, 10 = completely satisfied	Was the patient alive at 48 h after CVC removal? • Yes, no Date/time of death SAEs Results of CVC tip culture Results of CVC insertion site swabs Results of blood cultures

*APACHE* Acute Physiology and Chronic Health Evaluation, *CVAD* central venous access device, *CVP* central venous pressure, *ECG* electrocardiogram, *ICU* intensive care unit, *IHT* inter-hospital transfer, *IJ* internal jugular, *MARSI* medical adhesive related skin injury, *MLA* Mastisol liquid adhesive, *OT* operating theatre, *SAE* serious adverse event

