#### Secondary outcomes

All-cause CVAD failure: a composite of failure resulting in CVAD removal. Includes pain, infiltration/extravasation, blockage/occlusion (with or without leakage), fracture, thrombosis, dislodgement (complete or partial), or haematomaIndividual types of CVAD failure resulting in CVAD removal [pain, infiltration/extravasation, blockage/occlusion (with or without leakage), fracture, thrombosis, or dislodgement (complete or partial)]‘Central line associated bloodstream infection’ defined as per the National Healthcare and Safety Network (NHSN) [20]‘Primary bloodstream infection’ defined as per the NHSN [20]‘Local infection’ as defined by the Centres for Disease Control and Prevention (CDC)/NHSN ‘Arterial or venous infection’ criteria [21]Loss of dressing integrity not requiring dressing change (i.e. lifting at edges with/without reinforcement required) assessed for all dressings per patientDressing dwell time (from dressing application to removal in days) assessed for all dressings per patientPremature dressing removal (before seven days from dressing application; all dressings per patient)Number of dressing changes (from first application to last removal; all dressings per patient)Device dwell-time (time from CVAD insertion to removal in hours)Serious adverse events (i.e. mortality, CLABSI, MARSI)Adverse skin events relating to MARSI (e.g. pain, itch, erythema, skin stripping, blister, skin tear, irritant contact dermatitis, maceration, folliculitis or infection) [22]Cost (cost and number of products used, cost of treating complications, staff time for device insertion), as informed by standard diagnosis related groups (DRGs), staff time estimates to apply and remove dressings and product costs.Staff and patient satisfaction on dressing application and removal (0 = not at all satisfied to 10 = completely satisfied) assessed at initial application, all dressing changes and final removal for all dressing changes per patient.Skin colonization, measured both descriptively (i.e. organism) and quantitatively (i.e. colony forming units)

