#### Adverse event reporting and harms

Enrolled patients will be monitored and treated for untoward medical occurrences in line with standard clinical care. Therefore, only adverse events which the treating clinicians believe are associated with the intervention will be reported.

In this trial, the following will be considered as serious adverse events (SAEs):DeathCLABSIMARSI

All SAEs from randomisation to 48 h after removal of the CVAD will be recorded on REDCap and reported to the coordinating centre within 24 h.

The minimum information to report will include:Patient study numberNature of the eventCommencement and cessation of eventThe principal investigator’s assessment of the relationship between the study intervention and the event (not related, possibly related, probably related)Whether treatment was required for the event and what treatment was administered

It is the responsibility of each site’s principal investigator to inform the chief investigator and project manager of all SAEs which occur at their site. Copies of reports and correspondence to and from the reviewing HREC and research governance will also be sent to the coordinating centre. The project manager will be responsible for reporting all SAEs to the reviewing HREC and alerting other participating sites of the SAE if required.

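### The secondary skin-injury outcome depends on a judgement of cause by staff who know the arm, so differential attribution may create or hide a difference; an any-cause comparison should be pre-specified beside it

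*Protocol article*

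**What the plan says.** - **Outcome.** The Secondary outcomes section of the protocol article lists "Adverse skin events relating to MARSI", with example signs such as pain, itch, erythema, blister, maceration and infection, and a citation. The same list has a serious-adverse-event outcome that includes MARSI.
- **Data.** In Table 1 the daily check has one item for "Signs and symptoms of skin injury/reaction" and a separate item for "Suspected cause of MARSI or skin injury/reaction". The CVAD removal column records skin signs again and lists MARSI among the possible complications, but has no suspected-cause item.
- **Assessor.** Under Plans for assessment and collection of outcomes: "Research staff will perform daily assessments to collect data on the primary and secondary outcomes, protocol adherence and adverse events".
- **Blinding.** Under Who will be blinded: "blinding of patients/clinicians and research staff to the intervention is not possible". The statistician and the laboratory staff are blinded. For infection, "The infectious diseases consultant will also be blinded to treatment allocation when apportioning infection outcomes". Nothing comparable is given for skin events.
- **Inter-rater check.** It covers site and skin complications in a convenience sample of 8 patients per group, assessed by two research staff at one time point.
- **Stated limitation.** The Discussion says that lack of blinding may introduce performance bias. It does not mention bias in outcome assessment.

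**The concern.** MARSI stands for medical adhesive-related skin injury, so the outcome combines two things: a sign on the skin, and a judgement that an adhesive caused it. Many of the listed signs are non-specific, and the arms differ by exactly one extra adhesive. Knowing the arm therefore bears directly on the causal judgement. Staff may be readier to blame adhesive where the study product was used, or slower to do so if they favour the product.

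The abstract promises crucial data on skin injury, and the Discussion says evidence on skin reactions to the product is very limited. Readers are likely to rely on this trial's MARSI figures. If the arms differ on MARSI, or do not, the outcome alone cannot show whether the skin or the attribution is responsible. The primary outcome, dressing failure, is not touched by this point.

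**Working it through.** **1. Does the outcome need a causal judgement?** Yes. The outcome is restricted to events relating to MARSI, and the abbreviation list defines MARSI as adhesive-related.

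**2. Who makes it, and blinded to what?** Research staff assess daily and are not blinded. The only blinded clinical classification is for infection outcomes.

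**3. Would the inter-rater check show a bias?** No. Both raters are research staff, who are not blinded. Agreement and kappa measure whether they concur. A leaning that both share leaves agreement high.

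**4. Size, as an illustration.** The protocol gives no MARSI rate and no attribution share, so there is no figure to reproduce. All inputs below are assumptions except the 80 patients per arm and the 0.05 level, which are in the Sample size section (two-sided testing assumed).

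Recorded MARSI rate = rate of any skin sign × share attributed to adhesive. The chance of P < 0.05 is the exact binomial rejection probability of a two-sided pooled z test with 80 per arm.

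*Creating a difference (same true sign rate in both arms):*

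| Sign rate, both arms | Share attributed, control v MLA | Recorded MARSI, control v MLA | False difference | Chance of P < 0.05 |
|---|---|---|---|---|
| 15% | 50% v 60% | 7.5% v 9% | 1.5 points | 5.9% |
| 15% | 50% v 80% | 7.5% v 12% | 4.5 points | 15.6% |
| 30% | 50% v 60% | 15% v 18% | 3 points | 7.8% |
| 30% | 50% v 80% | 15% v 24% | 9 points | 30.1% |

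For example, 0.30 × 0.50 = 0.15 and 0.30 × 0.80 = 0.24. The false risk ratio is the ratio of the shares: 0.60/0.50 = 1.2 to 0.80/0.50 = 1.6. Reversing the shares gives a false benefit of the same size.

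*Hiding a difference:* suppose signs truly occur in 15% of control and 30% of MLA patients, and staff attribute 80% and 40% of them to adhesive. Recorded MARSI is 0.15 × 0.80 = 12% against 0.30 × 0.40 = 12%. The chance of P < 0.05 is 4.9%, against 63.5% if every sign were counted.

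*Any-cause count:* with equal sign rates of 15% or 30%, the chance of P < 0.05 is 4.8% or 5.1%. This holds only if signs are detected equally well in both arms.

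**The case against.** **No counting rule is stated.** A reader might infer from Table 1 that the suspected-cause item decides which events count. The documents do not support that. No sentence says so, the item can be read as asking for the cause of an event already classed as MARSI, and the removal column has no such item. This stands. What remains is that someone unblinded must judge relation to adhesive, by whatever route.

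**The definition is broad.** One might picture redness in a control patient being put down to infection, sweat or pressure and so dropping out. But the outcome list includes infection and maceration, and the Background adds pressure injuries to what CVAD-related MARSI typically covers. Relabelling of that kind need not remove an event. The outcome also cites a source not shown here, which may set sign-based criteria. This narrows the room for bias but does not close it, because the wording still requires a relation to MARSI.

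**Control patients have adhesive dressings too.** Standard dressings are used in both arms, so MARSI can be attributed in either. True; the issue is unequal attribution, and how unequal is unknown.

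**This is the adverse-event filter again.** A reader might infer that the reporting rule, "only adverse events which the treating clinicians believe are associated with the intervention will be reported", governs this outcome. It sits in the harms section, while the secondary outcome is collected at daily checks in both arms. The two should be kept apart.

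**The numbers are assumed, and signs are also seen unblinded.** Both stand. The low end of the illustration (5.9%) is practically nominal, the high end needs both the highest sign rate and the widest split, and an any-cause count removes only the attribution step.

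**Conclusion.** The point holds in a limited form. A secondary outcome rests on a causal judgement made by staff who know the arm, with none of the blinded classification given to infection outcomes and with an inter-rater check that cannot reveal a shared leaning. Differential attribution may create or hide a between-arm difference.

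Its size and direction cannot be told from the protocol. On the assumed inputs a false excess of 1.5 to 9 points is possible, with a 6% to 30% chance of P < 0.05; these figures show what could happen, not what is expected. It would be too strong to call this the trial's main skin-harm outcome, or to say that the result will be biased: the protocol ranks it only among the secondary outcomes and says nothing from which a bias could be measured.

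**What to change.** 1. Pre-specify, beside MARSI, a between-arm comparison of any skin sign or injury recorded at the CVAD dressing site at a daily check or at removal, whatever the suspected cause. Keep MARSI as an outcome and interpret a difference in it in the light of this comparison. If the two agree, attribution is a less likely explanation; if only MARSI differs, it is a plausible one.
2. Do not restrict the count to signs absent at enrolment. Table 1 records skin type, overall skin integrity and current wounds then, but no skin signs at the dressing site. Randomisation balances pre-existing signs on average.
3. In the Discussion, name assessment bias beside performance bias.

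The cost is one sentence in the outcome section, one row in the results table and one sentence in the limitations. The signs are already collected in both arms, and the sample size is unchanged. There are two downsides: signs unrelated to adhesive dilute the contrast, and unblinded detection of signs remains a limitation that this change does not cure.

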**Fig. 1 Fig1:**
[figure not shown]
SPIRIT figure

At the time of CVAD removal, research staff will collect procedural data, in addition to complications and treatment summary data. If able, patient reported satisfaction (see Secondary Outcome 14) will also be collected, in addition to a convenience sample of skin swabs (*n* = 10 per group) to assess skin colonisation under dressings (see Secondary Outcome 15). Patient outcome and adverse event data will be collected at 48 h after CVAD removal.

#### Plans to promote participant retention and complete follow-up

This study will have dedicated research staff every business day to collect relevant follow-up data for each patient. Clinical staff providing care to enrolled patients over the weekend will be provided education about the study protocol and adequate resources (i.e. MLA if applicable) for dressing changes over the weekend. Research staff will retrospectively collect as much data as possible from the patient’s medical notes and a study-specific bedside data collection log (documenting number of and reason for dressing changes) to complete the weekend data collection as fully as possible.

### Data management

Data will be entered either on to a hard copy data collection form and then transposed into an online Research Electronic Data Capture (REDCap) database [23, 24] or directly entered into the REDCap database. Each site will keep re-identifiable logs of all screened and recruited patients, in addition to an ‘investigator file’ (either electronic or hard copy) in line with ICH Good Clinical Practice requirements.

### Confidentiality

Patient confidentiality will be maintained at all times. Only research staff at each site will have access to identifiable patient information. All data entered into the REDCap database will be de-identified and only re-identifiable at the recruiting site using local screening and recruitment logs. Upon trial completion, only the statistician, project manager and local site principal investigators will have access to the de-identified data once exported from REDCap.

### Plans for collection, laboratory evaluation and storage of biological specimens in this trial and future use

Skin swabs will be collected from the area immediately surrounding the CVAD insertion site to assess micro-organism colonisation in a convenience sample of *n* = 10 per group occurring at either CVAD removal or dressing change if the CVAD has dwelled for three or more days. To do this, a sterile dry swab moistened with 0.9% saline will be firmly moved in a twisting back and forwards motion across the area immediately surrounding the CVAD insertion site. The swab will then be placed in a sterile container and transported to a nearby microbiology laboratory to be qualitatively and quantitatively cultured as per standard practice. After analysis, the swabs will be destroyed.

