**Methods:**

This two-arm, parallel group randomised controlled trial will be conducted in three Australian ICUs. A total of 160 patients (80 per group) will be enrolled in accordance with study inclusion and exclusion criteria. Patients will be randomised to receive either (1) ‘standard’ (in accordance with local hospital policy) CVAD dressings (control) or (2) ‘standard’ dressings in addition to MLA (intervention). Patients will be followed from the time of CVAD insertion to 48 h after CVAD removal. The primary outcome is ‘dressing failure’ defined as requirement for initial CVAD dressing to be replaced prior to seven days (routine replacement).

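### Skin colonisation is tested between arms as an effectiveness measure, but is measured only in a convenience sample of 10 per group taken by unblinded staff after allocation

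*Protocol article*

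**What the plan says.** Skin colonisation, by organism and by colony count, is the last of the 15 secondary outcomes in the protocol article. Four parts of the article bear on it.

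- **Selection.** The section on biological specimens plans swabs "to assess micro-organism colonisation in a convenience sample of" "10 per group occurring at either CVAD removal or dressing change if the CVAD has dwelled for three or more days". The data collection section repeats the convenience sample. No random, consecutive or hospital-balanced rule is given.
- **Collection.** The data collection section reads "At the time of CVAD removal, research staff will collect procedural data" and goes on, in the same paragraph, to list patient satisfaction "in addition to a convenience sample of skin swabs". It mentions removal only, whereas the specimens section also allows a dressing change.
- **Blinding.** Under Who will be blinded, "blinding of patients/clinicians and research staff to the intervention is not possible". By contrast, "microbiology laboratory staff will be blinded when culturing swab growth".
- **Analysis.** Under Statistical methods for outcomes, the rates of dressing failure, skin colonisation and CLABSI, with 95% confidence intervals, are to sum up how effective each arm is. Poisson regression tests the group difference, and P values below 0.05 count as significant. Colonisation carries no exploratory label.

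The trial "will be conducted in three Australian ICUs", each with its own standard dressing policy, and randomisation "will be stratified by patient sex to account for facial hair differences". Hospital is not a stratum.

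**The concern.** Randomisation makes the two groups of about 80 comparable. It does not do so for 10 patients per group taken by convenience once the arm is known. Blinding the laboratory protects the reading of the culture. It does not protect the choice of patient or the moment of swabbing.

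There are three routes to bias:

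1. **Choice of patient.** Staff who know the arm and can see the site may, without intending to, take different kinds of patient in the two arms.
2. **Hospital.** Nothing ties the swabs to hospital. If colonisation differs between hospitals and the arms draw on them in different proportions, a hospital difference appears as a treatment difference.
3. **Timing.** A dressing change is one of the two swab opportunities, and the adhesive is meant to make dressing changes rarer. Control swabs could come more often from lifting dressings, and intervention swabs more often from removals.

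At stake is whether a difference in colonisation, or a reassuring absence of one, can be read as a statement about the adhesive.

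**Working it through.** **The plan's own figure.** The protocol gives no power or precision for the swab comparison. Its only calculation is for the primary outcome: 50% v 25% failure, 90% power, significance level 0.05. The two-sided pooled-variance formula without continuity correction gives 77 per group, as stated, with power 0.901. That figure is sound and does not bear on the swabs.

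**Share sampled.** 2 × 10 / 160 = 12.5%.

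**Hospital mix.** Suppose there is no treatment effect and swabs come from two hospitals with colonisation rates pA and pB. Let s1 and s2 be the shares of each arm's swabs taken at hospital A. The expected false difference is

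(s1 − s2) × (pA − pB).

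The documents give none of these quantities, so all are assumptions:

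| Mix at A:B, one arm v the other | Rates 60% and 20% | Rates 50% and 30% |
|---|---|---|
| 6:4 v 4:6 | 0.2 × 0.4 = 8 points | 0.2 × 0.2 = 4 points |
| 7:3 v 3:7 | 0.4 × 0.4 = 16 points | 0.4 × 0.2 = 8 points |
| 8:2 v 2:8 | 0.6 × 0.4 = 24 points | 0.6 × 0.2 = 12 points |

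Taking A as the hospital with the 20% rate, the bottom row of the first column is 0.8 × 0.2 + 0.2 × 0.6 = 28% against 0.2 × 0.2 + 0.8 × 0.6 = 52%.

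**How likely such mixes are if picking ignores the arm.** With two hospitals contributing equally, the chance of 8 or more of 10 from one hospital is 56/1024 = 0.0547. The chance of 8:2 v 2:8 or worse, in either direction, is 2 × 0.0547² = 0.006. Milder imbalance is common: with three equal hospitals, the arms differ by 3 or more of 10 swabs at a given hospital with probability about 0.23 (two independent binomials, n = 10, probability 1/3). Chance imbalance of this kind adds noise rather than systematic bias, but a rule with equal numbers per arm within hospital removes it as well.

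**Timing.** The sample size section assumes initial dressing failure of 50% v 25%. If swabs at an early dressing change followed those rates, one would expect 10 × 0.50 = 5 in the control group and 10 × 0.25 = 2.5 in the intervention group. This is only an illustration, because failures before the third day of dwell would not qualify for a swab. It shows that the two arms' swabs need not be taken in the same circumstances.

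**Precision at 10 v 10.** Around 28% v 52% the approximate 95% half-width is 1.96 × √(0.28 × 0.72/10 + 0.52 × 0.48/10) = 0.42, or ±42 points. Fisher's exact test would call that false difference significant about 8% of the time. For 34% v 46% (the 12-point case) the figure is about 3%. The plan uses Poisson regression, so these two figures are indicative only.

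**The case against.** The strongest reply is that this is a small sub-study, openly labelled as a convenience sample, with equal numbers per group and a blinded laboratory. Its interval would be wider than any plausible bias. Most of that is fair: sample size limits this outcome at least as much as selection does, and no choice of rule changes 10 v 10. It does not explain why the outcome is then tested as a measure of effectiveness.

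A reader might also infer more than the documents support:

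- *That the comparison is no longer randomised.* All swabbed patients were randomised 1:1. What is lost is protection against selection after allocation.
- *That staff choose patients by arm.* The article says that research staff collect the swabs. That they also choose the patients is an inference, and nothing suggests that the arm guides them. The one staffing limit described, business-day cover, has no obvious link to arm.
- *That a 24-point bias is to be expected.* It needs assumed rates and an extreme split. The documents do not say how many hospitals will swab. If only one does, confounding by hospital is nil. Within a hospital, both arms get the same local standard dressing.
- *That colony counts have no common denominator.* The article gives one swabbing technique and location for both arms. An exact area is procedural detail that an article may leave to the full protocol.
- *That infection safety rests on these swabs.* CLABSI, primary bloodstream infection and local infection are outcomes for the whole trial, with a blinded consultant apportioning infections.

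Nor is the point merely something left to a fuller document. The article states how patients are selected, and an analysis plan cannot restore comparability after selection.

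**Conclusion.** The point holds in a limited form. A formal between-arm test of effectiveness is planned on 12.5% of patients, sampled by convenience after allocation by staff who know the arm, with two possible swab moments, one of which the intervention is meant to alter. The comparison therefore lacks the protection of randomisation.

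Bias is possible, not demonstrated, and its size cannot be derived from the documents. The 4 to 24 points above rest wholly on assumed hospital rates and mixes. The conclusion also rests on reading the data collection section to mean that the staff who collect the swabs influence who is swabbed. The primary outcome, its sample size and the other secondary outcomes are not affected.

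**What to change.** Replace the convenience sample with a rule that leaves no discretion once the arm is known. For example:

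- Swab the first consecutive patients in each arm, at each hospital that takes swabs, who meet the protocol's three-day dwell condition and have a swab opportunity on a business day.
- Take equal numbers per arm within each hospital.
- Use one common swab time point where possible, and make the data collection and specimens sections agree on it.
- Log every skipped patient with a reason.

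A flag set at randomisation would be less suitable, because whether a patient reaches the dwell condition is not known then.

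If the convenience sample is kept, report skin colonisation descriptively as exploratory and remove it from the effectiveness rates and the Poisson test.

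The cost is small: slightly slower accrual of the 20 swabs and a short log, with no extra swabs or staff. The rule reduces the bias but does not abolish it, since the dwell condition still depends on events after randomisation. The sample also remains small.
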